The present study aims to explore the effectiveness and cost-effectiveness of the CB group intervention described by Linton [22], modified for patients with knee OA. As far as we are aware, there have been no previous studies using this approach in patients with knee OA. The working hypothesis is that patients with symptomatic knee OA will benefit from this kind of CB rehabilitation program. More specifically, we intend to examine the effect of the intervention in terms of self-reported physical function and pain, pain-related work abstinence, the number of pain-related health care visits, and health-related quality of life (HRQoL). We also aim to determine the effect of the intervention on several psychological variables such as depression, anxiety, sense of coherence, pain catastrophizing, kinesiophobia, self-efficacy, and life satisfaction. Finally, we plan to run a cost-utility analysis of the intervention based on quality-adjusted life years (QALY).

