The patients will be randomly assigned to either the GP care and intervention group (n = 54) or the GP care control group (n = 54). Randomization will be conducted in blocks of six, separately for men and women. A computer-generated code for randomization will be constructed by a statistician who will not meet the study patients, and it will be administered via sealed opaque envelopes. The personnel responsible for data collection will be blinded to group assignment and will not be involved in providing the interventions. The code for randomization will be opened only after the statistical analyses have been performed after the 12-month follow-up point.

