### Statistical analysis

The mean (±SD) knee joint pain score (WOMAC, VAS) was estimated by using the results of the knee joint pain scores in previous studies [60,61]. Since the knee pain has to be ≥40 mm on a 100-mm VAS (WOMAC) in this present study, we postulated that there will be a mean of at least 48±16.2 mm in the WOMAC pain subscale at baseline. In our study the 20% reduction in primary outcome (WOMAC pain) due to the intervention was considered as being clinically relevant in accordance with the OMERACT-OARSI set of responder criteria [62]. In the comparison of the mean pain scores between the groups, 54 patients per group are needed according to a power calculation with the two-tailed Student t-test with a 5% significance level and 80% power, assuming a 20% dropout rate [63].

Demographic characteristics and baseline data will be summarized by descriptive statistics. Randomly missing data in the longitudinal set-up will be imputed using expectation–maximization algorithm before the analysis in order to follow the intention to treat principle. Data on various psychological variables predicting reported knee pain will be assessed by multiple regression analysis. For outcomes measured on a continuous scale, differences between groups in the mean change from the baseline to 12 months will be evaluated using the linear mixed modeling. The model assumptions will be checked by standard diagnostic plots. The participant rating of the global assessment of change will be compared between the two groups using the two-tailed Student t-test.

Cost-effectiveness of the intervention will be evaluated by cost-utility analysis which is a techniques that incorporates the expenses of the intervention as well as the costs of the use of health care services and pain medication, sick leaves, rehabilitation and pensions. Utility analysis is based on measurement of QALY from 15D [58]. Life expectancy with 0%, 3% and 5% discounting will be incorporated in the analysis. The cost-effectiveness of the intervention can be evaluated by dividing the overall costs with the QALY.

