## Discussion

There are several reasons why this study will advance our understanding of effective interventions to improve conservative knee OA treatment. First, there have only been a few studies evaluating the effect of psychological interventions on knee OA pain. Thus, good quality RCTs are needed to determine their effectiveness. As present, very few studies have evaluated a CB intervention for knee pain treatment, as far as we are aware this will be the first study to tackle this particular CB intervention model in treating OA patients. Second, the proposed research will address the very current topic of non-pharmacological conservative treatment of knee OA, and the results may have a significant impact on current care recommendations. Since knee OA is the most common form of arthritis, representing a major economic burden on social welfare and healthcare systems for both society and individual patients, it is worthwhile to find novel cost-effective interventions promoting conservative treatment. Third, it is important to evaluate this kind of CB intervention since cognitive and psychological factors are known to play major roles in chronic pain, pain severity and disability. Moreover, evidence-based guidelines indicate that one should adopt a the combination of pharmacologic and nonpharmacologic modalities to achieve adequate management of knee OA [64-66]. With respect to nonpharmacologic treatment modalities, it has been occasionally recommended that patients should participate in self-management programs with psychosocial interventions [64]. We hope that the results of the cost-effectiveness and cost-utility analysis of the proposed study will favour their inclusion into the current care recommendations in the future.

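### The stated cost-effectiveness measure, overall costs over the QALY, is an average ratio and does not give the incremental cost per QALY of adding the program to GP care

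*Protocol article*

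**What the plan says.** The Background section lists a QALY-based cost-utility analysis among the aims. The Statistical analysis section commits to it: "Cost-effectiveness of the intervention will be evaluated by cost-utility analysis". The costs to be counted are "the expenses of the intervention as well as the costs of the use of health care services and pain medication, sick leaves, rehabilitation and pensions". QALYs are to come from the 15D, and on the horizon the section adds: "Life expectancy with 0%, 3% and 5% discounting will be incorporated in the analysis". The paragraph then closes with the measure itself: "The cost-effectiveness of the intervention can be evaluated by dividing the overall costs with the QALY".

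The same section speaks of comparing groups for the pain scores, for continuous outcomes (mixed model) and for the global assessment of change (t-test). It does not do so for costs or for the ratio. Nowhere does the article mention a difference in cost, a difference in QALYs, QALYs gained, an incremental ratio or net benefit.

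Under Participants and recruitment, patients are randomised to GP care plus the program or to GP care alone, 54 per arm.

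**The concern.** Both arms receive GP care, so the economic question is what the program buys on top of it. That calls for a difference in cost set against a difference in QALYs.

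The stated measure contains neither. Its numerator includes care, sick leave and pensions that patients would have incurred anyway. Its denominator, taken at face value, includes QALYs that they would have accrued anyway. Such a ratio mostly describes how costly and how healthy the study population is.

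What is at stake is the economic conclusion. Cost-effectiveness is a stated aim and a listed secondary outcome, and the Discussion attaches policy weight to it: "We hope that the results of the cost-effectiveness and cost-utility analysis of the proposed study will favour their inclusion into the current care recommendations".

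**Working it through.** There is no plan figure to reproduce, because the article gives no cost, QALY or cost-per-QALY value. The check compares two estimators on assumed inputs.

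**Notation.** C0 and Q0 are mean cost and mean QALY under control; C1 and Q1 are the same under intervention. The stated measure, applied in an arm, is C/Q. The incremental ratio is (C1 − C0)/(Q1 − Q0).

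**Assumed inputs (12 months, arbitrary currency).** C0 = 2,000, Q0 = 0.80, extra cost 300, so C1 = 2,300. The control arm's average ratio is 2,000/0.80 = 2,500 throughout.

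| QALY difference | Stated ratio, intervention arm | Incremental ratio |
|---|---|---|
| −0.005 | 2,300/0.795 = 2,893 | costs more, yields less (dominated) |
| +0.005 | 2,300/0.805 = 2,857 | 300/0.005 = 60,000 |
| +0.01 | 2,300/0.81 = 2,840 | 300/0.01 = 30,000 |
| +0.02 | 2,300/0.82 = 2,805 | 300/0.02 = 15,000 |
| +0.05 | 2,300/0.85 = 2,706 | 300/0.05 = 6,000 |

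**Sensitivity to benefit.** From +0.005 to +0.02 the stated ratio changes by about 2% ((2,857 − 2,805)/2,857), while the incremental ratio changes fourfold. A program that loses 0.005 QALY gives 2,893, close to the values for programs that gain.

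**Sensitivity to background cost.** Raise C0 to 4,000 and keep the extra cost at 300. The stated ratio becomes 4,300/0.805 = 5,342 at +0.005 and 4,300/0.82 = 5,244 at +0.02. The incremental ratios stay at 60,000 and 15,000. Background cost moves the stated ratio far more than the program's effect does.

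**Setting the two arm ratios side by side.** For a positive QALY gain, C1/Q1 < C0/Q0 holds exactly when (C1 − C0)/(Q1 − Q0) < C0/Q0. The intervention arm therefore shows the lower ratio only if its incremental ratio falls below the control arm's own average ratio, here 2,500. That benchmark comes from background costs and health; no one has chosen it as a value for a QALY. In the last row of the table the arm ratios are 2,706 against 2,500, so the program appears unfavourable although its incremental ratio is 6,000. Neither the difference nor the quotient of the two arm ratios recovers the incremental ratio.

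**The case against.** The strongest reply is that the sentence is a loose gloss in a condensed article. It says only that the evaluation can be done this way, whereas the binding sentence commits to a cost-utility analysis of the intervention in a trial randomised against GP care. The QALY may be shorthand for QALYs gained, and the sponsor may well intend an incremental analysis. That is possible, but nothing in the article says so. Nor is this an omission that a fuller document would be expected to fill: a formula is stated, and it is the only one.

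Other parts of the reply stand.

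- A reader might infer that an expensive program with almost no benefit would look cheap. That follows only if the intervention arm's ratio is read alone against some outside threshold, and the article proposes none. Side by side, with an assumed extra cost of 600 and no QALY gain, the ratios are 2,600/0.80 = 3,250 against 2,500, so the program looks 30% dearer.
- A reader might also quote a multiple for the distortion. With an extra cost of 600 and a gain of 0.01, the incremental ratio of 600/0.01 = 60,000 is about 19 times the arm ratio of 2,600/0.81 = 3,210. That multiple rests wholly on assumed 12-month inputs. The article also says that life expectancy will enter the analysis, which these examples do not model.
- The absence of a bootstrap scheme, net benefit or acceptability curve is not a fault here, since an analysis plan commonly holds such detail. Resampling therapy groups would in any case be fragile: 54 patients in groups of 8–10 make only about 5 to 7 groups (54/10 = 5.4; 54/8 = 6.75).

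**Conclusion.** The point holds as a defect in the definition of the economic measure. As written, the ratio is an average one. Computed in each arm and compared, it still does not give the incremental cost per QALY of adding the program to GP care, so the cost-utility aim is not answered.

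The algebra behind this needs no assumed figures. The numbers show direction and sensitivity only, and no size can be given for this trial from the article. The documents do not establish that the sponsor intends to ignore the control arm, or that the result would favour the program. The stated ratio can mislead in either direction.

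The defect concerns a secondary outcome. Randomisation, the sample size and the primary WOMAC pain analysis are untouched.

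**What to change.** Replace the closing sentence of the economic paragraph with a definition such as: incremental cost-effectiveness ratio = (mean cost, intervention minus control) / (mean QALY, intervention minus control), reported with its uncertainty. The bootstrap scheme, and whether to add net benefit or an acceptability curve, can be left to the analysis plan.

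The cost is one sentence, settled before the economic analysis is run. The 15D and resource use are already planned in both arms at baseline, 3 and 12 months (Table 3 and Outcome assessment), so no new patient data are needed. The article does not list unit costs, but either form of the ratio needs them.

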## Discussion

There are several reasons why this study will advance our understanding of effective interventions to improve conservative knee OA treatment. First, there have only been a few studies evaluating the effect of psychological interventions on knee OA pain. Thus, good quality RCTs are needed to determine their effectiveness. As present, very few studies have evaluated a CB intervention for knee pain treatment, as far as we are aware this will be the first study to tackle this particular CB intervention model in treating OA patients. Second, the proposed research will address the very current topic of non-pharmacological conservative treatment of knee OA, and the results may have a significant impact on current care recommendations. Since knee OA is the most common form of arthritis, representing a major economic burden on social welfare and healthcare systems for both society and individual patients, it is worthwhile to find novel cost-effective interventions promoting conservative treatment. Third, it is important to evaluate this kind of CB intervention since cognitive and psychological factors are known to play major roles in chronic pain, pain severity and disability. Moreover, evidence-based guidelines indicate that one should adopt a the combination of pharmacologic and nonpharmacologic modalities to achieve adequate management of knee OA [64-66]. With respect to nonpharmacologic treatment modalities, it has been occasionally recommended that patients should participate in self-management programs with psychosocial interventions [64]. We hope that the results of the cost-effectiveness and cost-utility analysis of the proposed study will favour their inclusion into the current care recommendations in the future.

The study protocol has some limitations. First, due to volunteer bias, the results of psychological intervention studies may have limited generalizability [67]. Second, as the majority of the study patients will probably originate from primary care, the results of this study will mainly apply to that environment. Third, the CB protocol presented by Linton [22] indicates that patients participating in a CB-type intervention should be evaluated to ensure that they are at risk of developing a persistent pain problem. Linton himself has developed a questionnaire, the Örebro Musculoskeletal Pain Questionnaire (MPQ) [59], to be used for this purpose. In our study, however, we have decided not use this questionnaire or any other cognitive or psychological evaluation as part of the inclusion criteria. One reason for this decision is that the Örebro MPQ has only been validated in back pain patients, and there is a lack of data concerning the similarity of pain experiences in back and knee OA pain in general. Furthermore, our inclusion criteria already include several pain measures, assessing both intensity and duration of pain. We consider that by applying to these criteria, in all probability, the patients would be at risk of developing a persistent pain problem if they were not already suffering from it. However, the Örebro MPQ will be included in the baseline patient questionnaire for analysis purposes. With the availability of the final data of the study, it will be interesting to see whether those patients determined to be at risk of developing a persistent pain problem according to the Örebro MPQ have benefited more from this intervention.

Another limitation of the study might be the different amount of attention paid to the two groups. As the group of patients in the intervention will receive 12 hours more attention, a Hawthorne effect [68-70] is probable. However, all patients will receive the same basic instructions about knee OA treatment according to Finnish CC guideline [26] when they are listening to a lecture delivered by a general practitioner prior to the randomization. This lecture will be held in groups of about 20 people and the whole research group will be present to answer questions. During the lecture the patient-version booklet of Finnish CC guideline on knee and hip OA [26] will be handed out to all participants. The participants in both groups also will continue to receive standard care (i.e. normal routine care offered by their own general practitioners including analgesics and physiotherapy).

BDI-21, BAI, 13-item SOC scale, TSK, PSEQ and LS questionnaires have been used in several clinical studies in Finland [35-37,39,44-46,50,52-55]. However, at present BDI-21 and 13-item SOC scales have been validated in Finland [37,46] and the validation process of TSK is almost complete. We have available translated versions of separate questionnaires that have been in use in clinical studies and clinical routine in Finland. As the psychometric questionnaires are all secondary outcome measures in our study we decided to include them even though there is a shortage of supporting evidence for the validity of some of their psychometric measurement properties in Finnish patients.

Obtaining and assessing KL grades are not simple tasks. Valid measures are dependent on knee flexed standing views [71,72] and examiner experience [73,74]. Although it has recognized weaknesses, the KL score has been the most widely used radiographic score to assess knee OA [73]. We decided to use KL grade ≥2, which has been extensively used as the inclusion criterion in knee OA studies [33]. Unfortunately, we will not be able to control the radiographic quality since the knee X-rays will have been taken in public primary care locations and in the outpatient clinics. However, we use the combined radiographic and clinical criteria that have been proposed for use when diagnosing knee OA. If one combines the clinical and radiographic factors, the sensitivity and specificity of knee OA diagnosis are 91% and 86%, respectively [75]. The observers also will be well trained and acquainted with the radiographic atlas of the KL scores before the start any assessments. Although reliability for the separate KL radiographic features may depend on the level of the investigator’s experience, the intra- and inter-observer reliability for the overall score is known to be relatively high [74].

No significant side effects or adverse events are expected.
